### Standards for intervention delivery, process evaluation

Intervention implementation at each level will be monitored through ongoing process evaluation, with the intention of assuring that set standards are being met (Table 1). These standards are based on our review of the literature, and on our previous experiences implementing MLMC interventions in AI communities. The OPREVENT2 intervention team will meet every two months to review the degree to which intervention standards are being met, and will improve implementation on that basis.

**Table 1 Tab1:** Select process evaluation measures and standards by OPREVENT2 intervention component

Intervention level	Process evaluation measure	High standard^a^
Policy	# CAC meetings held/community/year # attendees/CAC meeting # different sectors represented/meeting	12 10 4
Schools	% teachers (grades 2–6) trained/school % lessons taught/grade % family packs returned	90 75 60
Food Stores	% promoted healthy foods stocked % shelf labels correctly placed # interactive sessions/store/phase # visitors/interactive session	80 80 6 20
Worksites	# participating worksites/community # coffee/water stations made over/participating community % AI staff initially participating in FitBit Challenge % AI staff participating in FitBit Challenge after 2 months	5 5 70 50
Community media	# radio announcements/week # newsletter/mailed flyers/phase	3 4
Social media	# Facebook, Instagram, Twitter posts/day/platform # boosts Facebook, Instagram, Twitter/week/platform # likes/follows/week/platform	3 3 50

^a^Quality of implementation based on % high standard met: low = <50%, med = 50–99%, high= > =100%

### Comparison communities (delayed intervention)

The comparison communities will receive the OPREVENT2 intervention following completion of the post-intervention evaluations.

### Data safety and monitoring

A Data Safety and Monitoring Board, meeting 1-2 times per year, has been formed to assure the study meets standards of safety and confidentiality, and to deal with possible adverse events.

### Measurements

The OPREVENT2 trial will be evaluated at each intervention level (Table 2). Process evaluation measures will assess reach, dose delivered, and fidelity of intervention implementation (Table 1).

**Table 2 Tab2:** Impact evaluation measures for the OPREVENT2 trial by intervention level

Intervention level	Impact/outcome measure
Policy	# CAC action items achieved/year # health-related issues put on tribal policymaker’s agenda/year Increase in CAC participant collective efficacy scores
Schools	# policy changes made to improve the school food and PA environments # structural changes made to improve the school food and PA environments (e.g., removal of vending machines)
Food Stores	# units of promoted foods sold # units of promoted foods purchased/consumed by OPREVENT2 participants
Worksites	# policy changes made to improve the workplace food and PA environments # structural changes made to improve the workplace food and PA environments (e.g., changing what’s in vending machines)
Adult/household	Household food purchasing (healthy and unhealthy foods) Healthiness of common methods of food preparation Change in psychosocial factors (knowledge, self-efficacy, intentions) Change in dietary patterns (e.g., total calories, total fat, FV servings, HEI scores, etc.) Change in PA (IPAQ, FitBit) Change in weight, BMI, blood pressure, waist and hip circumference

A sample of adults (100 per community) will be surveyed pre and post intervention to assess impact.

The Adult Impact Questionnaire (AIQ) will assess the food getting frequency of our promoted products, household patterns of food acquisition and preparation, adult PA, morbidity history and sociodemographic variables (e.g., age, education, income range). In addition, the AIQ will evaluate psychosocial constructs including healthy food knowledge, self-efficacy, intentions about food, and community resources/environment. The AIQ instrument uses a modified Individual Physical Activity Questionnaire (IPAQ) Short Form (IPAQ-SF). The IPAQ-SF specifically asks about walking, moderate-intensity PA, and vigorous-intensity PA. It was determined to be appropriate for this population and study for several reasons: validity studies have been conducted in similar populations; low time burden it was easy to modify to be more culturally acceptable for our target population; and it was piloted in the communities and found to be acceptable. Sociodemographic, family medical history and anthropometric measurements (i.e., height, weight, percent body fat, waist circumference, hip circumference, blood pressure, heart rate) will be collected to assess obesity and other health-related factors. We will be using Tanita 300GS (Tanita Corp., Tokyo, Japan) scales for body weight and percent body fat, and the Omron Fat Loss Monitor (HBF-306) will be used for a second percent body fat estimate. Blood pressure and heart rate will be measured using an Omron Automatic Wrist Blood Pressure Monitor, Model #BP652 (HEM-6052-Z), and will be assessed pre and post intervention in intervention and comparison respondents.

We worked with NutritionQuest to develop a modified Block Food Frequency Questionnaire (FFQ) specific to our study sample. In addition to standard Block FFQ food items, it includes traditional AI foods common in the Southwest and Upper Midwest regions, as well as specific food items promoted and de-promoted within our intervention. The FFQ was based on the FFQ that was used in the Strong Heart Study Family Study, Cardiovascular Disease in American Indians (Phase V), an instrument used by investigators at the Johns Hopkins Center for American Indian Health. The FFQ includes 95 questions pertaining to frequency and portion size of particular foods. Portion sizes will be estimated with the aid of standard portion size illustrations. The final section of the FFQ includes 24 questions pertaining to additions to food items (e.g., milk, creamer, etc. to coffee) and type of food items (e.g., low-fat, low-carb, etc.). The FFQ will be used to assess dietary intake pre and post intervention in intervention and comparison respondents.

At post intervention data collection, we will collect information on exposure to specific intervention components and materials for all participants which will be used to assess self-reported dose received by our evaluation sample.

A series of structured surveys will be conducted pre and post intervention in schools, food stores, and worksites to assess change at the level of these institutions in terms of the food and PA environments. A Community Action Component Impact Questionnaire will be administered to committee participants at their first meeting and at post intervention. Participant characteristics (e.g., age, occupation) will be gathered, and the instrument will be used to gauge change in collective efficacy, intentions, as well as a free list of community changes and feedback of CAC activities (post intervention only).

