### Participants and recruitment

The target group in the OPREVENT2 MLMC intervention is AI adults, ages 18–75 years. Participants in the evaluation sample will be randomly recruited from household lists provided by each tribe/community. Due to privacy concerns, in four of the communities, local authorities have agreed to provide us with randomly selected households. Once consent is received, interviews will be conducted with one person per household until 80 have been completed for each of the six communities. Potential participants will be screened for eligibility (e.g., tribal member, adult 18–75 years, no plans to move for next two years). If a randomly selected household is unable to complete the interview, then the next eligible household will be selected from the recruitment list.

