### Sample size and statistical methods

Sample size calculations were based on testing the change in mean BMI. Modeling and calculations were based on testing for an effect size d = |μ1–μ2|/σ = 0.5, where μ1 is the mean change in one of the two primary outcome measurements in the treatment group, μ2 is the corresponding mean change in the control group, and σ is the standard deviation of the observed differences. The detectable difference (|μ1–μ2|) for the change in mean BMI and daily FV intake was determined using the impact data from OPREVENT and other interventions similar to OPREVENT2. We used OPREVENT baseline BMI data on 422 AI adults to estimate the standard deviation of the observed differences between pre and post intervention BMIs, assuming that the variances of mean BMI from pre and post intervention are equal and assuming a large correlation between pre- and post-intervention measurements (*r* = 0.9). We used data from a survey sample of AIs in the Midwest [45] to estimate the standard deviation of the observed differences in mean daily FV under the same assumptions. For BMI, σ = 3.5 and therefore the detectable change in average BMI is 1.3 kg/m^2^. For FV, σ = 1.56 and therefore the detectable change in daily FV servings is 0.78 servings.

The power was obtained from a two-sample t-test formula β = 1 ‐ P(t ≤ t_α/2_) + P(t  ≤ ‐ t_α/2_), where t is a non-central t-distribution with df = 2(3–1) degrees of freedom and a non-centrality parameter NC = d/[2{1 + (85–1)ρ}/(3*85)]^1/2^. Here ρ is the within-community correlation between the differences between the primary outcomes. Calculations were based on a ρ equal to 0.01; this value is consistent with the range of correlations reported in the literature [46, 47] and the correlation for baseline BMI and FV found in OPREVENT. All calculations were done assuming a 20% loss to follow-up from pre to post data collection.

With 80 participants per community and three communities per arm, there is 80% power to detect an effect size of d = 0.5 (which corresponds to a 1.3 kg/m2 change in mean BMI and a 0.78 change in mean daily fruit and vegetable consumption) with a type I error of 5%.

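### The article gives three unreconciled sample sizes per community (80, 85 and 100), and the 85 in the power formula gives 87% power, not the stated 80%

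*Protocol article*

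**What the plan says.** The size of the evaluation sample per community appears in four places in the protocol article.

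- **Participants and recruitment:** "interviews will be conducted with one person per household until 80 have been completed for each of the six communities". A household that cannot take part is replaced by the next eligible one on the list.
- **Measurements** (below Table 2): "A sample of adults (100 per community) will be surveyed pre and post intervention to assess impact".
- **Sample size and statistical methods, formula:** "NC = d/[2{1 + (85–1)ρ}/(3*85)]^1/2". The cluster size enters twice, both times as 85.
- **Sample size and statistical methods, conclusion:** "With 80 participants per community and three communities per arm, there is 80% power to detect an effect size of d = 0.5".

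The last section also states "All calculations were done assuming a 20% loss to follow-up from pre to post data collection" and "Calculations were based on a ρ equal to 0.01". The article does not say how 80, 85 and 100 relate, or which of them are counted before loss and which after.

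**The concern.** One design should have one enrolled number and one analysed number per community, linked by the stated loss. Here there are three numbers, and the 20% loss does not link them. The figure in the formula exceeds the number at which recruitment stops, and loss to follow-up can only reduce that number.

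Two things are at stake. The first is the enrolment total: 6 × 80 = 480 or 6 × 100 = 600, a difference of 120 adults. A later reader could not tell whether 480 was full enrolment or 80% of target. The second is reproducibility: anyone who evaluates the formula as printed does not get the power that the article reports.

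**Working it through.** **Inputs**, all from Sample size and statistical methods unless noted: d = 0.5; ρ = 0.01; k = 3 communities per arm; df = 2(3 − 1) = 4; two-sided α = 0.05; loss 20%. Candidate sizes are 80 (Participants and recruitment, and the power sentence), 85 (formula) and 100 (Measurements).

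**Step 1. Apply the stated loss.**

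- 80 × 0.8 = 64
- 85 × 0.8 = 68
- 100 × 0.8 = 80

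Working back from 85 analysed: 85 / 0.8 = 106.25, so 107 enrolled, a number found nowhere in the article. Going from 100 to 85 would need a 15% loss, which is not stated. No loss rate turns 80 into 85.

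**Step 2. The plan's power formula.** With m analysed per community,

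NC = d / √[2{1 + (m − 1)ρ} / (3m)],

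and power = 1 − P(t ≤ 2.776) + P(t ≤ −2.776), where t is non-central with 4 df and 2.776 is the two-sided 5% critical value.

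**Step 3. Reproduce the stated 80%.** Take the power sentence with the stated loss, so m = 64: 1 + 63 × 0.01 = 1.63; 2 × 1.63 / 192 = 0.01698; square root 0.1303; NC = 0.5 / 0.1303 = 3.837; power 0.8145. This agrees with the stated 80% to within two percentage points.

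**Step 4. Evaluate the formula as printed.** With m = 85: 1 + 84 × 0.01 = 1.84; 2 × 1.84 / 255 = 0.01443; square root 0.1201; NC = 0.5 / 0.1201 = 4.162; power 0.8687.

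**Step 5. All candidates.**

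| m analysed | Where it would come from | NC | Power |
|---|---|---|---|
| 64 | 80 less 20% | 3.837 | 81% (0.8145) |
| 68 | 85 less 20% | 3.908 | 83% (0.8274) |
| 80 | 100 less 20%, or 80 with no loss | 4.094 | 86% (0.8584) |
| 85 | formula as printed | 4.162 | 87% (0.8687) |
| 100 | 100 with no loss | 4.341 | 89% (0.8932) |

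The smallest m that reaches 80% is 60 (0.8001).

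**The case against.** The strongest reply is that nothing of substance is lost. The only recruitment rule and the power conclusion agree on 80, and 80 less 20% reproduces the claimed power. The 100 is a single line under Measurements. Moreover 100 less 20% is exactly 80, so these two figures could be the before-loss and after-loss versions of one design.

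Much of this stands. It removes any claim that the trial is underpowered on this account. It does not remove the contradiction. The recruitment section uses 80 as the point where interviewing stops, which is a baseline count and not a completer count. The Measurements section has the 100 surveyed at both rounds, so it does not present 100 as a before-loss figure. If the 100-to-80 reading were right, power would be 86% and not 80%. On any of these readings 85 stays unexplained.

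Three stronger readings are tempting, and the article does not support them.

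- *A reader might infer that the trial falls about 25% short*, since 64 against 85 is a gap of 21. That needs 85 to be the intended analysed number, which implies 107 enrolled and 87% power. The article states neither.
- *A reader might infer that the 80% claim fits only 64 analysed.* That is the closest fit to a stated recruitment figure, but 68 (85 enrolled less 20%) gives 83% and 60 gives 80.0%.
- *A reader might infer that field staff hold two competing targets.* The article gives only one recruitment rule, at 80. The conflict is with a description elsewhere.

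That a journal article condenses a fuller protocol does not help here, because these are figures that the article itself states and that disagree.

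**Conclusion.** The point holds as an internal contradiction. The three sizes are not reconciled, 85 cannot be the analysed number from 80 or 100 with 20% loss, and the printed formula gives 87% where the text states 80%. The practical size is a 120-person ambiguity in total enrolment and a discrepancy of about 7 percentage points between formula and stated power. The stated power is met on every reading (81% to 89%), so this should be corrected but does not undermine the design.

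That reassurance rests on the article's own d = 0.5 and ρ = 0.01. At ρ = 0.015 the range is 75% (m = 64) to 82% (m = 100), and at ρ = 0.02 it is 69% to 76%. The choice of d is a separate question: the quoted BMI figures give 1.3 / 3.5 = 0.37, not 0.5, and at 0.37 power would be 58% to 68% over the same sizes. Neither dependence is caused by the conflict between 80, 85 and 100, and settling that conflict would not remove either.

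**What to change.** State one enrolled and one analysed number per community, and use the analysed number in the formula.

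- **On the plan's own recruitment rule:** 80 enrolled (480 in total) and 64 analysed after 20% loss. Replace 85 by 64 at both places in the non-centrality parameter, restate power as 81% for d = 0.5, and change 100 to 80 in Measurements.
- **If 100 was already the intended enrolment:** 100 enrolled (600 in total) and 80 analysed. Change the stopping point in Participants and recruitment to 100, put 80 in the formula, make the power sentence say 100 enrolled, 80 analysed and 86% power, and word Measurements so that 100 is the baseline number.

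The first option changes text in three places and adds no participants to the recruitment rule. The second is also a text change if 100 was always planned. Measured against the written stopping rule, it means 120 more adults.

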### Data safety and confidentiality

Electronically collected data will be encrypted using Secure Sockets Layer (SSL) encryption using REDCap and will be upload to a server at Johns Hopkins Bloomberg School of Public Health. All data collectors received a unique user PIN that are ciphered using Secure Hash Algorithm (SHA) cryptography, and all stored REDCAP data and REDCAP application logs are encrypted using advanced encryption standards on tablet PC until the data is uploaded. A separate administrator username and password will prevent data collectors from altering the data and data collection instruments.

### Sample size and statistical methods

Sample size calculations were based on testing the change in mean BMI. Modeling and calculations were based on testing for an effect size d = |μ1–μ2|/σ = 0.5, where μ1 is the mean change in one of the two primary outcome measurements in the treatment group, μ2 is the corresponding mean change in the control group, and σ is the standard deviation of the observed differences. The detectable difference (|μ1–μ2|) for the change in mean BMI and daily FV intake was determined using the impact data from OPREVENT and other interventions similar to OPREVENT2. We used OPREVENT baseline BMI data on 422 AI adults to estimate the standard deviation of the observed differences between pre and post intervention BMIs, assuming that the variances of mean BMI from pre and post intervention are equal and assuming a large correlation between pre- and post-intervention measurements (*r* = 0.9). We used data from a survey sample of AIs in the Midwest [45] to estimate the standard deviation of the observed differences in mean daily FV under the same assumptions. For BMI, σ = 3.5 and therefore the detectable change in average BMI is 1.3 kg/m^2^. For FV, σ = 1.56 and therefore the detectable change in daily FV servings is 0.78 servings.

The power was obtained from a two-sample t-test formula β = 1 ‐ P(t ≤ t_α/2_) + P(t  ≤ ‐ t_α/2_), where t is a non-central t-distribution with df = 2(3–1) degrees of freedom and a non-centrality parameter NC = d/[2{1 + (85–1)ρ}/(3*85)]^1/2^. Here ρ is the within-community correlation between the differences between the primary outcomes. Calculations were based on a ρ equal to 0.01; this value is consistent with the range of correlations reported in the literature [46, 47] and the correlation for baseline BMI and FV found in OPREVENT. All calculations were done assuming a 20% loss to follow-up from pre to post data collection.

With 80 participants per community and three communities per arm, there is 80% power to detect an effect size of d = 0.5 (which corresponds to a 1.3 kg/m2 change in mean BMI and a 0.78 change in mean daily fruit and vegetable consumption) with a type I error of 5%.

We will examine intervention effects by subtracting the pre intervention score/intake from post intervention score/intake and then conduct linear mixed-effect models for confirmatory testing of intervention effects. We will conduct t-tests for normally distributed continuous variables and nonparametric Wilcoxon-Mann-Whitney tests for non-normal continuous variables; Chi square and Fisher’s exact tests for dichotomous variables; and Mantel trend tests for ordinal variables. We will follow this exploratory analysis with multilevel mixed models using the lmer function from the lme4 package for R [48]. Linear and logistic regression models will be adopted for identifying intervention effects as well as risk factors in regression analyses. We will examine multiple primary response variables, including specific indicators of dietary quality (e.g., FV servings, energy intake) and of obesity (e.g. BMI). Fixed effects of the model will be baseline values for these variables, treatment group, age, gender, ethnicity and mediating variables wherever applicable. The community will be treated as a random effect.

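### The BMI detectable difference does not follow from its inputs: d = 0.5 with SD 3.5 is 1.75 kg/m², not 1.3, and at that SD power for 1.3 kg/m² is about 58%, not 80%

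*Protocol article*

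**What the plan says.** All the text is in the protocol article, under Sample size and statistical methods. The calculation is described as "testing for an effect size d = |μ1–μ2|/σ = 0.5", where "σ is the standard deviation of the observed differences" between pre and post measurements. For the two outcomes this is turned into natural units:

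- BMI: "For BMI, σ = 3.5 and therefore the detectable change in average BMI is 1.3 kg/m^2".
- FV intake: "For FV, σ = 1.56 and therefore the detectable change in daily FV servings is 0.78 servings".

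Power comes from a "non-central t-distribution with df = 2(3–1) degrees of freedom" and "NC = d/[2{1 + (85–1)ρ}/(3*85)]^1/2", with ρ = 0.01, a two-sided 5% test and 20% loss to follow-up. The closing statement, for 80 participants in each of three communities per arm, is that "there is 80% power to detect an effect size of d = 0.5 (which corresponds to a 1.3 kg/m2 change in mean BMI", with the FV equivalent alongside.

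**The concern.** Since d is the difference divided by σ, the detectable difference is d × σ. The FV line obeys this and the BMI line does not, although it is worded as a deduction from σ. The gap is 1.75 − 1.3 = 0.45 kg/m², too large for rounding. The same 1.3 reappears in the closing power statement, so a reader who goes only to that sentence takes away the inconsistent figure.

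The section says that the sample size was based on the change in mean BMI, so this is the figure on which the trial is sized. If the printed σ is right, the design is much less sensitive at 1.3 kg/m² than claimed, and a null BMI result would be given more weight against an effect of that size than it can bear. The Background reports that the precursor trial found no BMI change, so a null result is a realistic prospect.

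**Working it through.** **Inputs, all from the sample-size section.** d = 0.5; σ(BMI) = 3.5; σ(FV) = 1.56; three communities per arm; df = 2(3 − 1) = 4; ρ = 0.01; two-sided 5%, so the critical t is 2.776; 80 recruited per community and 20% loss, so m = 80 × 0.8 = 64 analysed. The printed formula uses 85 instead, so other values of m are shown too.

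**Step 1: conversion to natural units.**

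- FV: 0.5 × 1.56 = 0.78, as printed.
- BMI: 0.5 × 3.5 = 1.75, against 1.3 printed.
- In reverse: 1.3 / 3.5 = 0.371, not 0.5.
- SD needed for 1.3 to equal d = 0.5: 1.3 / 0.5 = 2.6.

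**Step 2: reproduce the plan's power.** NC = d / √[2{1 + (m − 1)ρ} / (3m)]. With m = 64:

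- 1 + 63 × 0.01 = 1.63
- 2 × 1.63 / 192 = 0.01698, square root 0.1303
- NC = 0.5 / 0.1303 = 3.84
- power = 81.5%

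This agrees with the stated 80%. Larger m gives 83% to 87%, so 64 analysed is the reading that best matches the plan.

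**Step 3: power for 1.3 kg/m² at SD 3.5.** NC = 0.371 / 0.1303 = 2.85, and power = 57.8%.

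| Analysed per community | Power, d = 0.5 | NC, 1.3 kg/m² | Power, 1.3 kg/m² | Difference with 80% power |
|---|---|---|---|---|
| 64 (80 less 20%) | 81.5% | 2.85 | 57.8% | 1.72 kg/m² |
| 68 (85 less 20%) | 82.7% | 2.90 | 59.2% | 1.68 kg/m² |
| 80 (no loss) | 85.8% | 3.04 | 63.0% | 1.61 kg/m² |
| 85 (as printed in the formula) | 86.9% | 3.09 | 64.4% | 1.58 kg/m² |

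The last three columns take σ = 3.5. The 100 per community given under Measurements, without loss, yields 67.9% for 1.3 kg/m². About 214 analysed per community would be needed for 80%.

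**Step 4: could another specification rescue 1.3?** Power near 80% for 1.3 kg/m² at SD 3.5 appears only if the stated method is abandoned:

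- a one-sided 5% test with no loss (80.0% at m = 80);
- a normal reference distribution in place of t with 4 df (81.3% at m = 64);
- ρ = 0 (79.8% at m = 68).

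None of these makes 0.5 × 3.5 equal 1.3.

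**Step 5: which figure is wrong?** σ was derived from baseline BMI with equal variances and r = 0.9, so σ = SD(baseline) × √[2(1 − 0.9)] = SD(baseline) × 0.447. Then σ = 3.5 implies a baseline SD of 3.5 / 0.447 = 7.8, and σ = 2.6 implies 2.6 / 0.447 = 5.8. The article does not print the baseline SD, so it cannot settle the question.

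**The case against.** The strongest reply is that the text proves an inconsistency, not that 1.3 is the wrong member of it. The SD of 3.5 is printed once and 1.3 twice. The section also says that the detectable differences drew on OPREVENT and similar interventions, so 1.3 may have its own source. If the SD of change is 2.6, then 1.3 is correct, d = 0.5 holds and power is about 81%. This stands: 1.75 and 58% are conditional on the printed SD. It does not remove the error, because the article presents 1.3 as following from 3.5 and as equivalent to d = 0.5. If 1.3 was fixed independently and σ is 3.5, the 80% claim fails outright.

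A second reply is that 58% depends on putting 64 into a formula printed with 85. That too is fair. The printed 85 gives 64%, which is still far short of 80%, and 64 is the reading that reproduces the plan's own figure.

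Thirdly, power for d = 0.5 is sound, the FV conversion is right, and no test, model or recruitment target changes. A null result should in any case be judged by its estimate and interval, not by planned power. All of this is true, and it limits the finding to the stated sensitivity for BMI. It is no reason to leave a power statement that contradicts its own inputs.

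**Conclusion.** The concern holds. The values d = 0.5, σ = 3.5 and 1.3 kg/m² cannot all be true, and the FV line shows which rule was intended. On the printed SD, the difference corresponding to d = 0.5 is 1.75 kg/m². Power for 1.3 kg/m² is about 58% at 64 analysed per community (up to 64% at the printed 85), so the type II error is about 42% where 20% is claimed. These results rest on the plan's non-central t with 4 df, ρ = 0.01 and SD 3.5. If the SD proves to be 2.6, the misprint is in the SD and the stated power survives.

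**What to change.** Recompute the SD of BMI change from the OPREVENT baseline data on 422 adults, and state the baseline SD it came from. Then:

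- **If 3.5 is confirmed:** replace 1.3 by 1.75 kg/m² in both places. State that power for 1.3 kg/m² is about 58% with 64 analysed per community. The value 1.72 kg/m² can be added as the difference with exactly 80% power at that size, but 1.75 is the one that corresponds to d = 0.5.
- **If the SD is 2.6:** correct the SD and leave 1.3 and its power as they are.

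In either case, say which number analysed per community the power refers to.

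The cost is one check of existing data and a correction of one or two figures. No participants are added and no analysis changes. If 3.5 stands, the stated sensitivity for BMI becomes less favourable.

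### The section on sample size names two primary outcomes, but its analysis paragraph opens the list to an unspecified number tested as confirmatory, so there is no closed primary family for the 5% to cover

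*Protocol article*

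**What the plan says.** Everything relevant is in the protocol article, under Sample size and statistical methods.

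- **Opening sentence.** "Sample size calculations were based on testing the change in mean BMI". Read alone, this points to one outcome.
- **Definition of the effect size.** The target is "effect size d = |μ1–μ2|/σ = 0.5", "where μ1 is the mean change in one of the two primary outcome measurements in the treatment group". The text then gives a standard deviation of change and a detectable difference for BMI and for daily FV servings, so these are the two.
- **Power statement.** With 80 participants per community and three communities per arm, it claims 80% power at d = 0.5 for both outcomes, with a 5% type I error.
- **Analysis paragraph.** "We will examine multiple primary response variables, including specific indicators of dietary quality (e.g., FV servings, energy intake) and of obesity (e.g. BMI"). The same paragraph says the team will "conduct linear mixed-effect models for confirmatory testing of intervention effects".

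The section states no ranking of the primaries, no division of the 5% and no rule that all must succeed.

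**The concern.** The number of primary outcomes goes from two to an unspecified plural within one section. Energy intake is added, and the words introducing the examples show that the list is not complete. Table 2 of the article shows how many variables could fit: under diet it lists total calories, total fat, FV servings and HEI scores, and under body size it lists weight, BMI, and waist and hip circumference.

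Because the mixed models are called confirmatory, these variables cannot simply be treated as exploratory. A reader of the results could not tell from this text which findings decide the trial, or over how many tests the 5% is meant to apply. The stated power is also tied to the number of primaries. It was computed with the whole 5% for one outcome, so any later rule that shares the 5% changes it.

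**Working it through.** **Inputs from the section.** Two-sided α = 0.05 (the formula uses the α/2 critical value and both tails); d = 0.5; three communities per arm; df = 2(3 − 1) = 4; ρ = 0.01; 80 enrolled per community; 20% loss, so m = 80 × 0.8 = 64 evaluable.

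**Step 1: reproduce the stated power.** The section's non-centrality parameter is NC = d / √[2{1 + (m − 1)ρ}/(3m)]. With m = 64:

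NC = 0.5 / √[2 × 1.63 / 192] = 0.5 / 0.1303 = 3.837.

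The non-central t with 4 df at two-sided 5% gives power 81.5%, which agrees with the stated 80%. Using m = 80 gives 85.8%, and m = 85, as printed in the formula, gives 86.9%. The 80% therefore rests on the full 5% for the outcome in question.

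**Step 2: the same calculation with the 5% shared (m = 64).**

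| Two-sided α per outcome | Power |
|---|---|
| 5% | 81.5% |
| 2.5% (two outcomes) | 64.8% |
| 1.67% (three outcomes) | 54.1% |

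**Step 3: chance of at least one false positive if any one primary counts and each is tested at 5%.** For k independent outcomes this is 1 − 0.95^k:

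- k = 2: 1 − 0.9025 = 9.75%
- k = 3: 1 − 0.8574 = 14.3%

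The article gives no correlation between outcomes, so a range was assumed. It was checked by simulating t-tests on three versus three community means:

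| Assumed correlation | Two outcomes | Three outcomes |
|---|---|---|
| 0.3 | 9.6% | 13.9% |
| 0.5 | 9.4% | 13.2% |
| 0.8 | 8.3% | 10.8% |

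**Step 4: power for two primaries under rules that hold 5% over the pair** (m = 64, d = 0.5 for both, independent outcomes).

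- *Holm, both effects real.* An outcome succeeds if its p is at most 0.025, or if its p lies between 0.025 and 0.05 and the other's is at most 0.025: 0.648 + (0.815 − 0.648) × 0.648 = 0.756, about 76% each.
- *Holm, one effect real.* 0.648 + (0.815 − 0.648) × 0.025 = 0.652, about 65%.
- *Fixed sequence.* First outcome 81.5%; second 0.815 × 0.815 = 0.664, about 66%.

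**Step 5: sensitivity to the BMI figures as printed.** The text states "For BMI, σ = 3.5 and therefore the detectable change in average BMI is 1.3 kg/m^2", and 1.3/3.5 = 0.37, not 0.5. That is a separate discrepancy, but it affects the choice of rule. At d = 0.37, BMI power is 57.8% at two-sided 5% and 40.1% at 2.5%. FV power behind a BMI gate is then 0.578 × 0.815 = 47%, against 0.648 + (0.815 − 0.648) × 0.401 = 71% under Holm.

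**The case against.** The strongest reply is that a multiplicity rule commonly sits in the analysis plan, that this is a journal article condensing a longer protocol, and that a trial registration is cited. This stands as far as it goes: the absence of an alpha rule is not in itself a fault here. It does not answer the contradiction, because the article states two different primary sets in its current text. Nor does it fully protect the power statement, since a plan that shares the 5% would no longer match it.

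Four stronger readings are tempting, and the article does not support them:

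- *That the stated 5% is false.* The article never claims 5% over a family, and never says that success on any one outcome is trial success. The 5% can hold per test.
- *That every variable in the analysis paragraph is tested at 5%.* The level is given only in the power statement, for BMI and FV. For energy intake and anything else it is an inference from the lack of another figure.
- *That the deciding outcome can be picked after the data are seen.* The registration and any analysis plan are not shown, and either may fix the list.
- *That BMI must be the sole or first primary because the trial was sized on it.* The section also derives a detectable difference and claims power for FV. The Background reports that the pilot found no BMI change but limited dietary effects, so a BMI-first order is open to debate.

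Independence is also doubtful where FV servings and energy intake both come from the food frequency questionnaire, which is why the correlated range is given. If both primaries had to succeed there would be no inflation, but joint power would be about 66% under independence. No such rule is stated.

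**Conclusion.** The point holds as a contradiction with a statistical consequence. The sample-size text fixes two primaries, each powered with a full two-sided 5%; the analysis paragraph replaces them with an open list tested as confirmatory. If any one success counts, the family-wise error is 9.75% for two and 14.3% for the three named outcomes under independence, and about 8–10% and 11–14% at assumed correlations of 0.3 to 0.8. These figures assume each outcome is tested at two-sided 5%, which the article shows for BMI and FV only. No figure is given for longer lists, because the text names no more than three variables. The contradiction is certain from the text. How far the error rate actually rises depends on a success rule the article does not state.

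**What to change.** In the analysis paragraph, name change in BMI and change in daily FV servings as the only primary outcomes, remove the 'e.g.' wording from that sentence, and make energy intake and all other diet and obesity indicators secondary. Add one sentence controlling 5% over the two primaries by a pre-stated rule, either Holm or a fixed sequence. The sponsor should choose the rule, and the order if there is one. Restate power for that rule, after reconciling the printed BMI difference with d = 0.5.

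The edit is one paragraph and needs no extra participants. Its price is a somewhat less favourable power statement under Holm (about 76% per outcome if both effects are real, 65% if only one is). Under a fixed sequence, the price is no confirmatory claim on the second outcome when the first fails. To keep 80% power with 2.5% for each outcome, the section's formula needs 127 evaluable per community, or 127/0.8, about 159 enrolled, which is roughly double the planned 80.
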